### Sample size {14}

In a previous study [24] in intensive care unit patients with muscle thickness as outcome, a baseline value of 11.2 mm (standard deviation (SD) of 2.7 mm) was observed with a reduction of 2.8 mm (SD 0.7 mm) in the control group vs. 2.1 mm (SD 0.9 mm) in the blood flow restriction group, with a sample size of 20 patients in each group. Using this as assumption in the sample size calculation, we set up a simulation study with R (version 4.2.2) to investigate the statistical power of an ANCOVA with Dunnett’s test to compare each of the three treatment arms to the control group. We assumed various scenarios for the standard deviation of the follow-up measurement from small (1 mm) over moderate (2 mm) to large (2.7 mm) as well as conservative to optimistic values for the correlation between baseline and follow-up measurement (rho between 0.7 and 1) (Fig. 3).

**Fig. 3 Fig3:**
[figure not shown]
Simulation results for the arm-specific power of an ANCOVA with Dunnett test based on 10.000 simulations

The simulation results indicate that under the assumption of a moderate standard deviation and relatively large correlation (rho > 0.9), a sample size of *N* = 30 per arm provides a statistical power of at least 75% for each arm, i.e., the marginal power. We view this as sufficient statistical power to explore the effectiveness of the different interventions for the first time under relatively conservative, and to be able to identify a promising treatment to be evaluated in a future trial.

### Recruitment {15}

The University Hospital Bonn has one of the largest surgical intensive care capacities in Germany (88 surgical intensive care beds). In the course of the feasibility study, all patients who meet the inclusion criteria can be enrolled in this study. To extend the inclusion to patients under sedation or mechanical ventilation, the consent to participate in the study by the “Ehegattennotvertretungsrecht” was also added and ethically confirmed. This allows the patient’s legal spouse, if they are not currently able to give consent, to be contacted and informed, and to confirm or decline participation in the study. During the pre-testing phase, a participation rate of 85% was achieved.

The feasibility of recruitment is derived from our experiences with the recruitment in previous intensive care projects. Approximately 3500 cases are treated at our institution’s surgical ICUs annually. Of these, approximately 5–10% have an extended stay < 7 days, making them good candidates for the proposed study. At the current rate of extended stay ICU patients, we expect to screen 25 patients per month. Of these we plan to recruit approximately 5–6 patients per month into the project, which means that in 36 months we can recruit up to 180 patients.

## Assignment of interventions: allocation

### Sequence generation {16a}

All patients included in the study will be randomized in one of our four study groups. Randomization is performed using a computer-generated block randomization list [33], using the statistical software R and the package"blockrand". The allocation is carried out according to the randomization list in numerical order of the pseudonyms. In order to obtain a balanced study design, two lists (pre- and post-interim analysis) will be created, each containing 30 patients per study arm. To avoid a bias by the participants, we have included a “Sham-Control” group which is receiving a “Sham-BFR/IPC” intervention with a fixed pressure of 20 mmHg to reduce the intervention bias. This also gives the patients in the control group the experience of taking part in an intervention.

#### Criteria for discontinuing or modifying allocated interventions

Drop-out of a patient from the study: One or more of the following circumstances may lead to a patient discontinuing the study (these patients are counted as drop-outs): Withdrawal of consent by the patients or their legal representatives without giving reasons; Occurrence of an exclusion criterion; Violation of the study protocol.

### Concealment mechanism {16b}

All potential participants will initially be screened for the eligibility criteria via physical examination on the ICU. Subsequently, all individuals who pass the initial screening and are interested in the study will sign a written informed consent and complete the baseline assessment. Following the baseline assessment, participants will be randomly allocated to one of the four study groups.

### Implementation {16c}

The results of the block randomization are printed out and distributed among 120 identical-looking, sealed letters numbered in ascending order from 1 to 120. The research assistants responsible for enrolment were not informed about the randomization list and accept the letters in order.

## Assignment of interventions: blinding

### Who will be blinded {17a}

Although full blinding of participants is not feasible due to the perceptible nature of the interventions (e.g., tourniquet pressure, electrical stimulation), a sham intervention protocol is employed to reduce performance and expectation bias.

Specifically, the control group receives a daily “Sham-BFR/IPC” procedure using a low, non-therapeutic pressure (20 mmHg), mimicking the setup and procedure of the BFR/IPC group without providing physiological stimulus. This approach ensures that participants experience a similar intervention environment and procedure across all groups, regardless of group allocation.

While participants may still perceive differences (particularly if conscious), the standardized application of equipment and procedures helps mitigate subjective bias. Outcome assessors and data analysts remain fully blinded to group assignments.

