**Methods:**

This prospective, randomized controlled trial will recruit 120 patients from the surgical ICU at the University Hospital Bonn, who meet the inclusion criteria of a > 48-h ICU stay. Patients will be randomized into four groups: Sham-Control, BFR/IPC, EStim, and combined BFR/IPC + EStim. The study’s primary endpoints include feasibility and safety metrics, such as patient compliance and stress response, alongside secondary endpoints related to clinical outcomes like ICU length of stay, ICUAW prevalence, muscle mass preservation, and rehabilitation efficacy. Measurements include non-invasive assessments of muscle mass, intramuscular microdialysis to monitor metabolic and inflammatory markers, and health-related quality of life evaluations post-discharge.

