#### Clinical feasibility, safety and acute muscle condition

To assess the clinical feasibility and safety of the applied interventions and diagnostic techniques on patients’ mental and physical health, the following endpoints are investigated in this study:*Feasibility*: Questionnaires regarding patient compliance (e.g., acute measure of recovery and stress, AEB) and possible stress response to the interventions (e.g., VAS 0–100 mm).*Global Health & Safety*: Changes in drug application for supporting the cardiovascular system (e.g., noradrenaline), use of analgetic (e.g., fentanyl) and sedation drugs (e.g., propofol) and changes in respiratory gases before, during and after each intervention session. Daily assessment of inflammation and coagulation parameters.

Since ICUAW and the resulting complications in the process of rehabilitation can be attributed to compromised muscle health, specific outcome parameters were selected that allow an objective description of possible positive or negative effects of the course of therapy, applied interventions, and further hospitalization on skeletal muscle conditions. These parameters will be partially recorded daily or before and after the intervention period, as well as by discharge from the ICU and hospital:*Muscle Health*: Muscle mass and fiber angle, muscle strength, neuromuscular activation, body composition (by bioelectrical impedance analysis).

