
(3)In-exercise measurements
Physical and Mental Responses to Interventions:In order to analyze the impact of the interventions on patients mental and physical condition, before, each 10 min of exercise and after exercise, vital parameters such as blood pressure, pulse and oxygen saturation are measured. Furthermore, each from the beginning of the exercise intervention, each 10 min the applied medications for cardiovascular support, pain relief, and sedation are determined. For assessing the compliance of the patients to the interventions, subjective pain and exercise intensity will be obtained by visual analog scale (0–100 mm) and acute measure of recovery and stress (Akutmaß, Kurzskala, [32]).Blood Gas AnalysisBefore and after the exercise, a capillary blood sample is taken to visualize the venous blood gases (vBGA). The vBGA is used to determine carbon dioxide partial pressure (pCO_2_), oxygen partial pressure (pO_2_), oxygen content (ctO_2_), oxygen saturation (sO_2_), oxyhemoglobin fraction (FO_2_Hb), hemoglobin content (ctHb), oxygen half-saturation pressure (p50) and the concentration of lactate ([La^−^]), potassium ([K^+^]), sodium ([Na^+^]), calcium ([Ca^2+^]), bicarbonate ([HCO_3_^−^]), and chloride ([Cl^−^]).Intramuscular MonitoringDuring training interventions, the flow rate of the microdialysis catheter will be increased to 2 µl/min to get each 10 min a volume of 20 µl for analyzing the acute effects of the training interventions on muscle metabolism.

All outcome measures, there metric and timepoints are listed in Supplementary Table 2.

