### Procedure for unblinding if needed {17b}

In this study, only outcome assessors are blinded to group allocation. Participants and clinical staff are not blinded due to the perceptible nature of the interventions.

Unblinding of outcome assessors will only take place if required for participant safety or in exceptional circumstances affecting data validity. Any such unblinding will be initiated and documented by the principal investigators.

Data analysts will receive only anonymized and already unblinded datasets after completion of data collection. Since no interim analyses are planned, unblinding of data analysts during the trial is neither necessary nor possible.

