#### Data acquisition

All patients will undergo the standardized study protocol. Before the start of the project, research assistants will be trained to standardized protocols to obtain the outcome parameter. Per each day, each measurement will be repeated thrice per time point. The median of these technical replicates will be used as the repeated measurement value for said time point.

All outcome data will be collected using standardized data collection forms. These forms are paper-based and will be completed manually by trained research staff during or immediately after each measurement or intervention session.

The collected data will then be entered into a secure, password-protected instance of REDCap (Research Electronic Data Capture), hosted at the University Hospital Bonn. Access to REDCap is restricted to authorized study personnel.

To ensure data completeness and accuracy, the following quality assurance measures are in place:All study personnel are trained in data collection protocols before study initiation.Each measurement is performed three times, and the median is used for analysis.Data entry is performed by one investigator and checked by a second member of the research team (dual entry control).REDCap includes validation rules and logic checks to minimize entry errors.Monthly internal audits will be performed by the principal investigators to identify missing or inconsistent data.

All changes in the database are tracked automatically and time-stamped to ensure full auditability.

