## Oversight and monitoring

### Composition of the coordinating center and trial steering committee {5d}

This is a single-center, investigator-initiated trial without a formal trial steering committee or coordinating center.

The trial is managed and overseen by the principal investigators (Dr. med. [name] and PD Dr. med. [name]), who are responsible for overall study coordination, protocol adherence, safety oversight, and communication with the ethics committee.

The day-to-day conduct of the trial, including patient recruitment, intervention delivery, and data collection, is managed by the research team from the Departments of Anesthesiology and Intensive Care Medicine and Orthopedics and Trauma Surgery at University Hospital Bonn.

Weekly internal meetings are held to monitor study progress, discuss any issues, and ensure compliance with study procedures and timelines.

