### Adverse event reporting and harms {22}

#### Adverse events and serious adverse events grading

## Adverse event grading

Adverse events will be graded using standard criteria. Relationship of event to the study procedure will be determined by the study physician.GRADE 1 (Mild) Transient or mild discomfort (< 48 h); no medical intervention/therapy requiredGRADE 2 (Moderate) Mild to moderate limitation in activity—some assistance may be needed; no or minimal medical intervention/therapy requiredGRADE 3 (Severe) Marked limitation in activity, some assistance usually required; medical intervention/therapy required, hospitalizations possibleGRADE 4 (Life-threatening) Extreme limitation in activity, significant assistance required; significant medical intervention/therapy required, hospitalization or hospice care probable.

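### The unqualified claim of fully blinded outcome assessors cannot hold for the in-session feasibility and safety outcomes or for adverse events

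*Protocol article*

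**What the plan says.** On blinding, section {17a} makes one unqualified statement: "Outcome assessors and data analysts remain fully blinded to group assignments". Section {17b} again says that outcome assessors are blinded, then adds: "Participants and clinical staff are not blinded due to the perceptible nature of the interventions".

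On endpoints, the abstract says that the "primary endpoints include feasibility and safety metrics, such as patient compliance and stress response". The Objectives section (Clinical feasibility, safety and acute muscle condition) fills this out. Feasibility is compliance questionnaires and stress response. Safety is changes in cardiovascular, analgesic and sedative drugs and "changes in respiratory gases before, during and after each intervention session", together with daily inflammation and coagulation values.

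On collection, the in-exercise part of Outcomes {12} says that "before, each 10 min of exercise and after exercise, vital parameters such as blood pressure, pulse and oxygen saturation are measured". It puts medications on the same 10-minute schedule, and takes VAS pain and exertion and the recovery/stress scale as the measure of compliance. Under {18a}, Data acquisition, the paper forms are "completed manually by trained research staff during or immediately after each measurement or intervention session". Section {5d} says that the day-to-day conduct, "including patient recruitment, intervention delivery, and data collection, is managed by the research team".

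On harms, the reporting procedures under {22} have clinical staff record the events they observe. The grading section adds: "Relationship of event to the study procedure will be determined by the study physician".

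**The concern.** Assessor blinding is a design property that readers use to judge risk of bias. Here it is asserted for every outcome, yet the outcomes that the abstract calls primary are largely gathered at the bedside around or during a session in which the allocated treatment is in plain view. If the sentence stands, a reader could take the feasibility and safety conclusion as resting on blinded assessment when much of it is open-label. The items most open to influence are those with judgement or prompting in them: VAS and recovery/stress ratings, whether an event is noticed and written down, and whether it is attributed to the procedure.

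Feasibility and safety are the main conclusions of this trial and are meant to inform a multicentre study. Section {21a} provides no separate monitoring. An accurate account of how these data were obtained therefore matters more than usual.

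**Working it through.** No figure in the plan bears on this, so there is nothing to recompute. The check is to take each type of outcome and ask who records it, what that person can see, and whether the statement in {17a} can be true.

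**What is visible during a session.** Sections {6b} and {11a} put the cuff at 20 mmHg in the sham and EStim arms and at 100% of limb occlusion pressure in the other two. Four stimulation electrodes on the thigh (two on vastus lateralis, two on vastus medialis) are described for the EStim protocol, which is used in two arms only. Someone recording data in the room can see whether electrodes are in use and how the cuff is being operated.

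**Outcome by outcome.**

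1. *Drug changes.* Named as a safety endpoint in the Objectives and recorded every 10 minutes in session under {12}. The forms are filled in by hand during or just after the session. The recorder can see the arm, so the claim fails.
2. *VAS and recovery/stress ratings.* Named as feasibility endpoints. The rater is the participant, and {17b} says participants are not blinded. The claim fails whoever holds the form. The 10-minute schedule is stated for vital signs and medications, not for these ratings.
3. *Vital signs.* Recorded every 10 minutes in session, so equally open. Neither the abstract nor the Objectives section lists them by name as primary. They enter through {12} and through adverse-event monitoring under {22}.
4. *Adverse-event capture.* Section {22} has clinical staff record events and {17b} says clinical staff are not blinded. This is the plainest contradiction, because two explicit statements cannot both stand beside the one in {17a}.
5. *Adverse-event relatedness.* Judged by the study physician, for whom no blinding is stated.
6. *Blood gases and daily laboratory values.* Results come from analysed samples. Knowing the arm has little scope to change them.
7. *Day-7 ultrasound, strength and EMG.* Not measured during a session, so blinding is possible. Section {14} bases the sample size on muscle thickness, and {20a} gives an ANCOVA on the day-7 measurement, so this is the measure for which real masking is worth most.

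**The analyst half of the same sentence.** Section {17a} says data analysts are fully blinded, and Data analysis under {19} likewise says the biostatistician is blinded. Section {17b} says that only outcome assessors are blinded and that analysts receive datasets that are already unblinded. These statements cannot all be correct.

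**The case against.** The best reply is that the article already discloses the open status. Section {17b} says that participants and clinical staff are not blinded, and these are the sources of the ratings and of the adverse-event records. That is fair, and it means the document does not hide the fact. It does not rescue {17a}, which makes no exception. Nor does it cover drug recordings written down in session by research staff.

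Three stronger readings are tempting, and the documents do not support them.

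- *That none of the primary endpoints is protected.* The safety set includes laboratory values and blood gas results, for which assessor blinding matters little.
- *That the person who delivers the session is the person who assesses the outcome.* Section {5d} places both tasks with one team drawn from two departments. It does not say one individual does both. A separate observer in the session would still see the arm, so the in-session point stands without this inference.
- *That the day-7 muscle assessment is in fact unblinded.* Sections {17a} and {17b} say the assessors are blinded, and {17b} restricts and documents any unblinding. Skin redness under {22} is a potential event, and every arm wears a cuff, so a cuff mark alone would not identify the arm. Rotas and image handling are also details that an article may leave to the full protocol.

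Finally, that results will be reported as blinded-assessor evidence is a risk created by the wording. Nothing in the document says that they will be.

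**Conclusion.** The statement in {17a} is wrong as written. It cannot hold for in-session drug recordings, for VAS and recovery/stress ratings, or for adverse-event capture, and nothing in the article supports it for relatedness. In-session vital signs are open-label for the same reason. It can hold for day-7 ultrasound, strength and EMG, and it matters little for laboratory and blood gas results. The analyst statement in the same sentence is contradicted by {17b}.

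The conclusion rests on two things: the article's own account of who records what and when, and the assumption that a person recording in the room can see the electrodes and the cuff being operated. It does not rest on any claim that bias will occur or in which direction. Counting the in-session readings would not measure bias either. The consequence is a misstated design property for a large part of the primary feasibility and safety set, which should be corrected. It does not invalidate the trial.

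**What to change.** Replace the blanket wording in {17a} and {17b} with blinding stated by endpoint.

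1. State that in-session drug, vital-sign, VAS and recovery/stress data, and adverse-event capture and relatedness, are open-label. Interpret the feasibility and safety conclusion accordingly.
2. Limit the blinded-assessor claim to ultrasound, strength and EMG, and to telephone follow-up where uninvolved staff do it. Have these measured by an existing team member who neither opens that patient's allocation letter nor attends that patient's sessions. Code the ultrasound images before software post-processing.
3. Reconcile {17a}, {17b} and Data analysis under {19} on the analysts: state one position on whether they are blinded and until when.

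The cost is small: protocol wording, minor rota planning within the existing team, and a stated level of blinding that is less favourable than the present one. No patients are added and no treatment changes. The article gives the trial status as in preparation, so on that status the change can be made before data collection.

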### Procedure for unblinding if needed {17b}

In this study, only outcome assessors are blinded to group allocation. Participants and clinical staff are not blinded due to the perceptible nature of the interventions.

Unblinding of outcome assessors will only take place if required for participant safety or in exceptional circumstances affecting data validity. Any such unblinding will be initiated and documented by the principal investigators.

Data analysts will receive only anonymized and already unblinded datasets after completion of data collection. Since no interim analyses are planned, unblinding of data analysts during the trial is neither necessary nor possible.

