#### Data analysis

For each study arm and time point the pooled median values will be compared against the control group and the other respective study groups. The data analysis is carried out by a blinded biostatistician.

After trial completion and data analysis, the pseudonymization list will be destroyed, and data will be converted to fully anonymized form.

All anonymized data will be archived for 10 years in accordance with institutional and national data retention policies for clinical research. The data will be stored on institutional servers with secure backup and will be deleted irreversibly after the retention period.

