## Statistical methods

### Statistical methods for primary and secondary outcomes {20a}

#### Data acquisition

All patients will undergo the standardized study protocol. Per each day, measurements will be repeated thrice per time point. The median of these technical replicates will be used as the repeated measurement value for said time point. For descriptive purposes values will be reported as median ± interquartile range or absolute number and percent, where appropriate.

Primary analysis method will be an ANCOVA with Dunnett’s test with the measurement after 7 days as outcome and adjusted for the baseline value. Additionally, mixed models will be fitted to assess the sensitivity of the results under consideration of all measurement points. Health-related quality of life will be analyzed using mixed models for repeated measurements. Again, joint models may be considered to take a considerable proportion of missing data into account. Time-to-event outcomes, such as length of ICU stay, length of hospital stay, and time to return to work, will be analyzed using Kaplan–Meier estimates and Cox regression models.

All primary, secondary, and other exploratory outcomes will also be reported descriptively. Patients who decide to drop out of the study prior to completion of the intervention will remain in the study analysis and their respective study cohort following an intention-to-treat analysis. Recruitment will commence until the overall number of 120.

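### The protocol contradicts itself on whether data analysts are blinded, so a blinded analysis cannot be relied on

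*Protocol article*

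**What the plan says.** Three sections of the protocol article bear on whether the analyst knows the allocation.

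- Who will be blinded {17a}: "Outcome assessors and data analysts remain fully blinded to group assignments".
- Procedure for unblinding if needed {17b}, the section that follows directly: "In this study, only outcome assessors are blinded to group allocation". It then says of the analysts: "Data analysts will receive only anonymized and already unblinded datasets after completion of data collection". It closes with: "Since no interim analyses are planned, unblinding of data analysts during the trial is neither necessary nor possible".
- Data management {19}, under Data analysis: "The data analysis is carried out by a blinded biostatistician".

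The statistical methods section {20a} matters for any repair, because it fixes the main method: "Primary analysis method will be an ANCOVA with Dunnett’s test with the measurement after 7 days as outcome and adjusted for the baseline value". Dunnett's test compares each active arm with one reference arm, so whoever runs it must know which arm is the reference.

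**The concern.** Two sections present analyst blinding as a feature of the trial. The section between them leaves analysts out of the blinded group and describes a hand-over of data in which the allocation is already open. A reader cannot tell which procedure the trial will follow.

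Participants and clinical staff are not blinded, as {17b} itself states. What remains is blinding of the outcome assessors and, if it exists, of the analysts. The trial compares three active arms with sham, partly to choose an arm worth taking into a later trial (Sample size {14}). Blinding the analyst keeps knowledge of the arms out of any judgement still to be made during the analysis. If the results paper cites {17a} or {19} while the work was done under {17b}, it will report a safeguard that was not in place.

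**Working it through.** No arithmetic applies: the point depends on no rate, effect size, standard deviation, alpha or sample size. The check is a comparison of the statements.

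**Step 1. Sort the statements.**

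| Section | Analyst status |
|---|---|
| {17a} | Blinded, without qualification |
| {17b}, first sentence | Not among those blinded (outcome assessors only) |
| {17b}, on hand-over | Receives unblinded data once collection has ended |
| {17b}, last sentence | Not unblinded during the trial |
| {19}, Data analysis | Blinded while carrying out the analysis |

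Two statements say that the analyst is blinded, in {17a} and {19}. Two say the opposite, both in {17b}. The last sentence of {17b} concerns only the period before hand-over.

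**Step 2. Try the readings that would remove the conflict.**

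1. *Blinded during the trial, unblinded at hand-over.* This fits the last sentence of {17b}. It does not fit the first sentence of {17b}, which leaves analysts out altogether. Nor does it fit {19}, which places the blinding at the analysis itself; analysis starts after hand-over, when under {17b} the labels are visible.
2. *The word unblinded is a slip for blinded.* This would reconcile the hand-over sentence with {17a} and {19}. The first sentence of {17b} would still limit blinding to outcome assessors, so one contradiction would remain. A slip would need correcting in any case.
3. *Anonymization stands in for blinding.* Anonymization removes the identity of the patient. It does not remove the arm label.

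None of the three clears every statement.

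**Step 3. Look for a rule of precedence.** The article gives none. {17a} is the section on who is blinded, {17b} is the section on unblinding, and {19} is the section that describes the analysis. Each has some claim to be the governing text.

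**Step 4. Check {17a} against the main method.** Dunnett's test needs the sham arm to be identified. So even if {17a} prevails, full blinding of the analyst must be qualified for that one code.

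**The case against.** The strongest reply is that this is a drafting error. Two of the three sections agree that the analyst is blinded, one of them being the section on the analysis itself, and the end of {17b} suggests that analysts have no access to the allocation while the trial runs. This is plausible, and it is a good reason not to assume the worst. It does not remove the conflict, because two separate sentences of {17b} point the other way.

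A second reply is that the trial keeps other protections: blinded outcome assessors, a sham procedure, sealed numbered letters for allocation, and a stated baseline-adjusted ANCOVA at day 7. The article also says that the trial is not sized for firm conclusions on efficacy. All of this stands, and it limits how much weight the point can carry.

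Two stronger readings are tempting, and the document supports neither.

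- *That the blinded analysis will not take place.* This follows only if {17b} is the text that is followed, and nothing gives it precedence over {17a} and {19}.
- *That the missing-data decisions will be taken with the arm labels visible.* Sections {20a} and {20c} leave the use of joint models and multiple imputation conditional on the extent and type of missing data. A statistical analysis plan that is not shown may settle those choices, and the amount of missing data can be judged without arm labels. This inference therefore needs two assumptions: that {17b} governs, and that no other document fixes the choices.

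**Conclusion.** The point stands as an internal contradiction. {17a} and {19} claim a blinded analyst; {17b} limits blinding to outcome assessors and gives the analyst unblinded data after collection ends. Since the article does not say which text governs, a blinded analysis cannot be relied on. If {17b} is followed, the claim in the other two sections is false.

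The consequence is a possible loss of one stated protection against bias, and no figure can be put on it. Alpha, power and sample size are unaffected. The conclusion rests on the article's wording alone and needs no assumption about the analysis plan: a plan that agreed with one section would still contradict another. It is worth correcting before data exist, and the article gives the trial status as in preparation.

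**What to change.** Reconcile the three sections.

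- **{17b}:** state that, after data collection, the analyst receives a locked dataset in which the four arms carry neutral codes. The sham code is disclosed only as the reference for Dunnett's test, once the analysis script is fixed. The remaining codes are opened after the main results have been produced. Amend the first sentence so that it no longer limits blinding to outcome assessors.
- **{17a}:** replace full blinding of analysts with a statement that they work on coded arms, with the sham code disclosed as above.
- **{19}, Data analysis:** use the same wording.

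If the sponsor does intend an unblinded analysis, the claims of a blinded analyst in {17a} and {19} should be removed instead. That also resolves the contradiction, at the price of giving up the safeguard.

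The cost of the first option is a few sentences and a coded arm variable prepared by someone other than the analyst who holds the randomization list. The downside is minor data handling. No change to design, sample size or analysis method is needed.
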